**3a. Primary outcomes**

Aim 2: Cluster randomized controlled trial (cRCT)

The primary outcome for this study is **Mean change in depression scores, anxiety scores and trauma scores** measured longitudinally (5 measures) over 12 months as follows:

- Depressive symptoms: Using the Patient Health Questionnaire (PHQ-9)
- Anxiety symptoms: Using the Generalized Anxiety Disorder-7 (GAD-7)
- Trauma symptoms: Using the Child and Adolescent Trauma Screen (CATS) for AYHIV <18 years and the PTSD checklist for DSM-5 (PCL-5) for AYHIV ≥18 years

**3b. Secondary outcome**

Aim 2: Viral suppression among AYHIV (secondary effectiveness outcome)

- Measured from abstracted clinic records and defined as viral load of <200 copies/ml.

Primary and secondary effectiveness outcomes are summarized in table 1

| **Table 1: Primary and secondary effectiveness outcomes** | | | | | |
| --- | --- | --- | --- | --- | --- |
| **Condition** | **Tool** | **Number of items** | **Validated age group** | **Time points for assessment** | **Scoring criteria** |
| ***Primary outcomes*** | | | | | |
| Depression | PHQ-9/M | 9 items | 12+ years | Baseline, 3, 6, 9, 12 months | No depression (0-4)  Mild depression (5-9)  Moderate depression (10-19)  Severe depression (≥20) |
| Anxiety | GAD-7 | 7 items | 12+ years | Baseline, 3, 6, 9, 12 months | No anxiety (0-4)  Mild anxiety (5-9)  Moderate anxiety (10-14)  Severe anxiety (≥15) |
| Trauma symptoms | CATS  PCL-5 | 20 items  20 items | 7-17 years  18+ years | Baseline, 3, 6, 9,12 months | ≥21 is clinically relevant  ≥31 is clinically relevant |
| ***Secondary outcomes*** | | | | | |
| Viral suppression | N/A | N/A | N/A | Baseline, month 6, month 12 | <50 copies/ml: Undetectable  <1000 copies/ml: Suppressed |

- Aim 2: Implementation and service outcomes are summarized in table 2

| **Table 2. Description of implementation outcomes as per Proctor's IOF and Glasgow's RE-AIM, measurement approach & frequency** | | | | |
| --- | --- | --- | --- | --- |
| **Implementation outcomes** | **Specific outcome** | **How to measure** | **When to measure** | **Data source** |
| **Reach** | Screening for anxiety and depression | Proportion of AYHIV in intervention vs control clinics routinely screened using the PHQ-2/PHQ-9 tool out of total AYHIV who should be screened | Early (month 3) and late (month 12) implementation | Patient records |
|  | Linkage to psychological intervention | Proportion of AYHIV in intervention vs control enrolled in the psychological intervention among those diagnosed with anxiety and/or depression |  |  |
| **Adoption** | Initiation of PRO-ACT intervention | Proportion of intervention clinics that participated in the PRO-ACT initial training and elected to deliver PRO-ACT | End-line | Study records |
| **Implementation / fidelity** | Fidelity to PRO-ACT | Proportion of intervention clinics implementing PRO-ACT with high fidelity. Assessed using a standardized checklist and self-report | Early (month 3) and late (month 12) implementation | Checklist |
| **Maintenance** | Screening for anxiety and depression | Proportion with sustained screening practices (% of AYHIV with a routine PHQ-2/9 at each visit) | Late (at month 12) implementation covering up to 12 months of adolescent treatment | Routine clinic patient records |
|  | Delivery of PRO-ACT intervention | Proportion with sustained treatment practices (% of AYHIV eligible for PRO-ACT with any PRO-ACT modules completed at each visit) |  | Checklist & patient records |
| **Acceptability** | Acceptability of PRO-ACT | Acceptability of PRO-ACT among AYHIV and providers in intervention clinics, assessed quantitatively and qualitatively | Early (month 3-6) and late (month 12) implementation and post-trial | Survey with HCW and post-trial FGDs and IDIs with HCW and AYHIV |
| **Appropriateness** | Appropriateness of PRO-ACT | Appropriateness of PRO-ACT among AYHIV and providers in intervention clinics, assessed quantitatively and qualitatively | Early (month 3-6) and late (month 12) implementation and post-trial | Survey with HCW and post-trial FGDs and IDIs with HCW and AYHIV |
| **SERVICE outcomes** | | | | |
| **Satisfaction with services** |  | Adolescent satisfaction with services received | Baseline and late implementation (at month 12) | Survey with enrolled adolescents |
| **Competency assessment** |  | ENACT assessment for providers | Pre-training, post-training, post-supervision | ENACT through EQUIP platform |
| **Self-efficacy** |  | Provider self-efficacy with implementing PRO-ACT | Baseline, month 3-6 and month 12 | Survey with HCW |
| **Provider satisfaction** |  | Provider satisfaction with services they offer, with the PRO-ACT training and supervision | Baseline, Post-training, and Post-supervision | Surveys with providers |

Aim 3: Economic evaluation

This aim will assess the following measures:

- Cost of PRO-ACT provider training and implementation
- Incremental cost-effectiveness: net added cost per case of depressive/anxiety/trauma symptoms resolved (health outcome)

*Additional exploratory outcomes*

- Cost per additional adolescent or youth with HIV with ≥80% adherence
- Cost per additional adolescent or youth with HIV virally suppressed

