**Aim 2: Evaluate the effectiveness and implementation of PRO-ACT for AYHIV ages 16-24 years.**

Approach: We will conduct a hybrid 1 effectiveness-implementation cluster randomized control trial in 30 HIV clinics. We will select and randomize 30 adolescent HIV clinics in Nairobi, Kisumu, and Homa Bay counties, and train non-specialist providers in 15 intervention sites. We will optimize the delivery of PRO-ACT in the intervention sites in a 6-month pretrial period using continuous quality improvement processes. Primary effectiveness outcome: Reduction in depressive, anxiety and trauma symptoms among AYHIV. Secondary outcome: Viral suppression among AYHIV. Implementation outcomes: Compare reach and describe adoption, fidelity / implementation, maintenance, acceptability and appropriateness. Identify determinants of reach, fidelity, and maintenance. Service outcomes: satisfaction of training by providers and satisfaction with services by AYHIV and providers.

*Hypothesis: The intervention will result in a significantly larger reduction of depressive, anxiety and trauma-related symptomatology over 12 months compared to the standard of care. Implementation of the intervention will improve the reach and maintenance in mental health screening and management for AYHIV.*

**Aim 3: Determine cost and cost-effectiveness of implementation for PRO-ACT training, delivery, and implementation process.**

Approach: We will conduct a time-driven activity-based costing of the intervention’s implementation strategies (training and implementation in clinics) within the 30 clinics in Kenya participating in the study to estimate the implementation costs from a patient and health system perspective. We will in addition utilize the health outcome data based on the health outcome of the intervention’s implementation in the 30 sites to estimate cost effectiveness or the intervention.

*Hypothesis: There will be an increase in costs related to the training and time for providers offering mental health services and a reduction in projected costs related to poor HIV-related and mental health. The incremental cost effectiveness ratio of the interventions will be positive.*

1. **STUDY OUTCOMES**

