| AIM 2: Assess implementation and service outcomes and determinants of implementation |  | FGDs with providers | Up to 30 with 7-10 participants each from the intervention and control facilities ≥18 years old |
|  |  | IDIs with providers | Up to 6 IDIs with providers from each participating clinic |
|  |  | FGDs with AYHIV | Up to 30 with 7-10 participants 16-24 years each from intervention facilities |
|  |  | Competence assessments using the ENACT tool | Up to 90 trained providers ≥18 years old at the 15 intervention clinics |
|  |  | Fidelity assessments using a standardized checklist | Up to 90 trained providers ≥18 years old at the 15 intervention clinics |
|  |  | Quantitative surveys with AYHIV | ~600 AYHIV involved in the intervention |
|  |  | Routine clinic records for AYHIV | All AYHIV in the 30 clinics ages 16-24 years |
|  |  | Checklist in the patient chart | All AYHIV (~2400) AYHIV 16-24 years in the study sites |
|  |  | Quantitative survey with facility/HIV clinic heads | 30 facility/ HIV clinic heads from selected study sites |
|  |  | Quantitative surveys with providers | Up to 6 providers from each of the 30 selected study sites |
| Aim 3: Conduct an economic evaluation of the intervention |  | Time in motion studies for provider time | Providers in the 30 adolescent HIV clinics |
|  |  | Interviews with program officers with information on program administration | 30 program officers in the HIV clinics |
|  |  | Quantitative surveys with AYHIV | ~600 AYHIV involved in the intervention |

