**7f. Assessing implementation of the intervention**

To assess the implementation of the intervention, the study will conduct the following procedures (summarized in Table 2).

Patient records will provide data on mental health screening using PHQ2/9 for AYHIV in 30 clinics, 6-months prior to the start of the study, and up to 24 months after site entry. These data will inform assessments of **reach** (~2400 records) and **maintenance** (~1200 records).

A checklist will be developed and will accompany patient charts (~2400 charts) and completed by clinic staff to assess implementation/fidelity of mental health screening. In the intervention sites (~1200 charts), the checklist will also be used to assess **implementation/fidelity** focusing on adherence to PRO-ACT by providers for ~300 AYHIV. Another checklist will be completed by the supervisors assessing **implementation/fidelity** during the review sessions with providers after completing PROACT sessions with study participants.

Study administrative records for the 15 sites will be used to track which study sites are trained and elect to deliver PRO-ACT, informing assessment of **adoption**.

A survey with providers in the intervention sites (~6 per site) will assess **readiness** to implement PRO-ACT, **acceptability**, **appropriateness** of PRO-ACT, **satisfaction** with services offered and the PRO-ACT training, and **determinants of implementation**. Those in the control sites will rate their **satisfaction** with services they offer AYHIV.

A survey with facility heads will assess structural **readiness** to implement PRO-ACT, barriers and facilitators to implementation and describe HIV and mental health **resources** and processes in the facility.

For trained providers in intervention sites (~6 per site), their **competence** pre-training, immediately after training and after completing supervision will be assessed using the WHO, EQUIP-developed ENACT provider competency assessment tool, within the virtual EQUIP platform. The providers will role play sessions with standardized patient actors trained using standard vignettes, which will be rated by study-trained raters within the study (following standardized/established EQUIP procedures as used in the Nairobi pilot of PRO-ACT).

Adolescent **satisfaction** with mental health services offered in clinics and cost of care, acceptability and appropriateness of PRO-ACT will be assessed using a survey.

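### Fidelity is defined only as a yes/no on 15 clinics with no stated cut-off, which discards the finer checklist data and leaves low power for any quantitative analysis of its determinants

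*Protocol*

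**What the plan says.** Section 3b, Table 2, has one row for fidelity, measured at months 3 and 12: "Proportion of intervention clinics implementing PRO-ACT with high fidelity. Assessed using a standardized checklist and self-report". It states no rule for rating a clinic as high. Section 2b (Aim 2) has the team "train non-specialist providers in 15 intervention sites", so 15 clinics enter the proportion.

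The data collected are finer than that:
- Section 7f describes a chart checklist in the intervention sites "focusing on adherence to PRO-ACT by providers for ~300 AYHIV".
- Section 7f adds a second checklist, completed by supervisors "during the review sessions with providers after completing PROACT sessions with study participants".
- Table 3 (section 5d) lists "Fidelity assessments using a standardized checklist" for "Up to 90 trained providers ≥18 years old at the 15 intervention clinics".
- Section 11a has providers logging modules started and completed at each visit, and has both providers and study staff completing fidelity checklists.

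On purpose, Aim 2 says "Compare reach and describe adoption, fidelity / implementation, maintenance, acceptability and appropriateness", and then "Identify determinants of reach, fidelity, and maintenance". Section 12c says record- and provider-level analyses of implementation outcomes will use random coefficient models for clustering within site, with covariates and interactions examined.

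**The concern.** Turning checklist data into one yes/no per clinic loses two things: differences between providers and sessions within a clinic, and the degree to which clinics differ from each other. What remains is 15 binary values, cut at an unstated point.

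Two uses suffer. The descriptive proportion will have a wide interval. Any quantitative look at what drives fidelity will have low power, and it cannot examine provider characteristics within clinics at all, because every provider in a clinic shares one value.

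There is also a mismatch inside the protocol. The section 12c model for record- and provider-level data has nothing to work on when the outcome is one binary value per clinic. Reach, and the delivery part of maintenance, are defined in the same table as proportions of youth, so a finer level for fidelity would not be out of keeping.

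**Working it through.** **Inputs from the protocol.** 15 intervention clinics; about 300 youth, so 300/15 = 20 per clinic; up to 90 providers, so 90/15 = 6 per clinic; alpha 0.05 (taken as two-sided), power 0.80 and R² 0.05 for implementation outcomes (section 12a).

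**Assumed, because the protocol gives no figure.** A clinic-level determinant splits the clinics 7 against 8. The intraclass correlation (ICC) of fidelity is 0.05 to 0.30.

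**1. The plan's nearest figure.** Section 12a, Table 6 (minimum detectable effects), gives Cohen's d = 1.03 for a continuous site-level outcome on 30 sites. With J sites and one value each, the variance of the difference is 4 × (1 − R²)/J = 4 × 0.95/30 = 0.1267, SE 0.356. A two-sided noncentral t with 28 df reaches 80% power at d = 1.033, so the figure reproduces. It is for 30 sites; fidelity to PRO-ACT exists in 15, and no figure is given for that.

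**2. Precision of the clinic proportion.**
- 12 of 15 (80%): Wilson 95% interval 0.548 to 0.930.
- 9 of 15 (60%): exact 95% interval 0.323 to 0.837.

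**3. Power on the yes/no outcome.** Exact power of Fisher's test, 7 clinics at the first rate and 8 at the second:

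| High fidelity | Power |
|---|---|
| 40% vs 80% | 0.31 |
| 50% vs 90% | 0.31 |
| 30% vs 80% | 0.47 |
| 20% vs 80% | 0.65 |
| 20% vs 90% | 0.83 |

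Putting the lower rate in the group of 8 instead gives 0.27 for the first row. A gap of roughly 70 percentage points is needed for 80% power.

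**4. A graded measure on the same clinics.** For a clinic-level determinant, SE = √{[ICC + (1 − ICC)/m] × (1/7 + 1/8)} in total-SD units, with 13 df.
- Example, m = 6 and ICC 0.1: √{[0.1 + 0.9/6] × 0.2679} = 0.259. The detectable difference at 80% power is 0.78 SD.
- Over ICC 0.05 to 0.30: 0.72 to 1.01 SD with 6 providers per clinic, and 0.49 to 0.91 SD with 20 youth per clinic.

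**5. Same clinic means, kept as a score or cut at the midpoint** (simulation, 6 per clinic, t-test against Fisher's test):

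| True difference | ICC | Score | Cut |
|---|---|---|---|
| 0.5 SD | 0.05 | 0.51 | 0.34 |
| 0.5 SD | 0.30 | 0.29 | 0.18 |
| 0.8 SD | 0.05 | 0.88 | 0.68 |
| 0.8 SD | 0.10 | 0.81 | 0.60 |
| 0.8 SD | 0.30 | 0.59 | 0.39 |

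A second set-up gives the same picture: a continuous determinant correlated 0.6 with clinic fidelity, 20 youth per clinic, ICC 0.1 to 0.3, about 60% of clinics rated high. Power is about 50 to 64% on the score and 30 to 41% on the cut. With sessions nested in providers the gain at that correlation is still about 15 to 25 points.

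**6. Provider-level determinants.** With 45 against 45 providers varying within clinics, SE = √[(1 − ICC) × 2/45]. At ICC 0.1 this is 0.20, and the detectable difference is 0.57 SD (0.50 to 0.58 SD over ICC 0.05 to 0.30). The clinic yes/no cannot address this question.

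**The case against.** The case on the other side has real substance.

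- **Fidelity is to be described.** Aim 2 says so, and its hypothesis names reach and maintenance, not fidelity. A clinic proportion is a reasonable descriptive summary. This stands, and is why the proportion should be kept.
- **Determinants are studied mainly by qualitative means.** Sections 7f and 12a assign them to interviews and focus groups, with thematic saturation as the justification. A reader might infer from the power figures that the aim of identifying determinants will fail. The protocol does not support that: the figures bear only on a quantitative analysis. Such an analysis is in view, since section 7f gives the provider survey a determinants component and section 12c examines covariates, but no section says high- and low-fidelity clinics will be compared.
- **Section 12c already foresees finer models.** True, so it would be wrong to say the plan forces every fidelity analysis onto the binary outcome. But those models cannot be applied to the outcome as Table 2 defines it.
- **No checklist score is written down.** Also true. The protocol mentions checklists, with no scoring, averaging or threshold, and the scoring detail could sit in a statistical analysis plan. What the protocol itself fixes is the level and form of the outcome.
- **Fifteen clinics are the main limit.** This stands for clinic-level determinants: even the score needs about 0.5 to 1.0 SD.
- **Modules vary by client.** Section 6 gives psychoeducation to everyone and selects the rest by symptoms, so a fixed list of required elements would be wrong. The fix has to allow for this.

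**Conclusion.** The point holds in limited form. Table 2 fixes fidelity as an uncut-off yes/no on 15 clinics, although finer data are already to be collected. The descriptive result will be imprecise (55% to 93% at 12 of 15). A quantitative determinant analysis on it has about 31% power for a 40-point difference. In the settings in step 5 where clinic means are kept rather than cut at the midpoint, power rises by about 11 to 21 points, and a provider-level measure opens questions that the clinic value cannot address.

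These sizes rest on the assumed 7 against 8 split, the ICC range and the effect sizes; none is in the protocol. The interval for 12 of 15 needs only the clinic count and an illustrative result. The matter concerns an implementation outcome and does not touch the primary effectiveness comparison.

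**What to change.** In Table 2, define fidelity as the percentage of applicable checklist elements delivered, per session or per provider, at months 3 and 12. Make the denominator specific to the client: psychoeducation plus the modules selected for that client under section 6.

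In section 12c, analyse this measure with the random coefficient model already named (session or provider within clinic), and use it for any quantitative work on determinants. Keep the proportion of high-fidelity clinics as a descriptive summary, with its cut-off stated in advance and an interval based on 15 clinics. Where section 12a quotes site-level detectable effects, note that fidelity has 15 sites, not 30.

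The cost is a written scoring rule, including how the choice of modules is handled, and wording changes in Table 2 and section 12c. The checklists are already planned, though their items should be checked against the scoring rule before use. A percentage of elements is slightly harder to communicate than a count of clinics, which is still reported.

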**4.** **STUDY DESIGN**

This study uses a hybrid type 1 cluster randomized clinical trial to evaluate the effectiveness of the PRO-ACT intervention to reduce depressive, anxiety and trauma-related symptoms, and study the implementation and cost of the intervention. A cluster RCT is suitable as the intervention will be implemented at the clinic and provider level rather than exclusively at the individual AYHIV level. The adaptation and optimization phase will ensure that the intervention is relevant and suitable for delivery in the HIV clinic, with all relevant providers in the intervention clinics trained on PRO-ACT.

**5. STUDY ENROLLMENT AND WITHDRAWAL**

**5a. Study sites**

The stakeholders’ workshop and the subsequent refinement of PRO-ACT will be coordinated at a centralized site in Nairobi. The pretrial contextual adaptation of PRO-ACT, and the cluster randomized controlled trial (cRCT) will be conducted in 30 HIV clinics selected from two counties – Nairobi, Kisumu and Homa Bay counties in Kenya.

**5b. Study population**

The stakeholders’ workshop will involve policymakers, frontline providers, researchers, adolescents and youth with HIV and their caregivers. Non-specialist providers in adolescent HIV clinics selected to participate in the study and randomized to intervention sites will be trained on PRO-ACT and will administer the intervention. Providers in both intervention and control sites will also participate in the implementation of the study. Adolescents and youth ages 16-24 years in the selected intervention and control clinics will be eligible to participate in the study.

**Justification for involvement of adolescents:** In sub-Saharan Africa, adolescents living with HIV are at high risk for poor mental health and poor treatment outcomes. This study aims to address adolescent mental health and HIV care. The data from this study will be used to assess the effectiveness of the psychological intervention, its implementation and cost effectiveness in adolescent HIV care settings.

**5c. Participant inclusion criteria**

Eligibility is summarized in table 3. Participants in the stakeholders workshop will be adults except for the 2 minors (<18 year olds) in the group representing AYHIV. Non-specialist providers ages 18 years and above employed in the selected adolescent HIV clinics will be eligible for training (if in intervention sites) and other study procedures in both intervention and control sites. All AYHIV ages 16-24 years in the selected sites will be eligible to participate in the study (including abstraction of their clinic data and completing surveys), while those with symptoms of psychological distress following screening in the intervention sites will be eligible for the PRO-ACT intervention. The HIV clinics will be selected from among the public facilities in Nairobi, Kisumu and Homa Bay counties with at least 100 adolescents and youth ages 10-24 years in care, and no other psychological intervention being tested in the clinic.

**5d. Site/Participant exclusion criteria**

A facility may be excluded if there are barriers to conducting provider training or data collection/ abstraction. Individuals will be excluded if any study procedure would put them at an increased risk or if their compliance with study procedures is not possible. Adolescents below 16 years will be excluded since we expect that majority of them will require additional interventions targeting caregivers since they have not achieved independence in care, and have not been fully disclosed to their HIV status. This younger age group therefore requires a separate study with an intervention adapted to their needs.

| **Table 3: Populations involved in the study** | | | |
| --- | --- | --- | --- |
| **Aim** | **Design** | **Approach/strategy and data source** | **Participant numbers and inclusion characteristics** |
| AIM 1: Adapt and optimize the training on PRO-ACT and the intervention delivery | Cross-sectional | Stakeholder workshop | 40 stakeholders including policymakers, frontline providers, researchers, representatives of adolescents and youth with HIV (AYHIV) and other community members |
|  |  | Continuous quality improvement (CQI) of PRO-ACT delivery in 15 public HIV clinics selected for the cluster randomized trial as intervention sites | Approximately 120 providers ≥18 years old at 15 intervention clinics (up to 6 per site trained on the PRO-ACT intervention); and up to 6 AYHIV age 16-24 years per site. |
| AIM 2: Test effectiveness of the PRO-ACT intervention | Cluster randomized trial | 30 public HIV clinics each with at least 100 AYHIV | AYHIV age 16-24 years attending public HIV clinics. We expect ~2400 AYHIV will be screened and ~300 AYHIV with mild to moderate psychological distress will be followed-up in each arm, with the ~300 in the intervention clinics receiving the intervention |
|  |  | Survey assessing provider satisfaction with training | Up to 90 trained providers ≥18 years old at 15 intervention clinics (up to 6 per site) |
|  |  | Surveys | All AYHIV (~2400) ages 16-24 years in the 30 participating clinics will be screened using mental health assessment tools in a survey.  The ~300 AYHIV followed up in each arm will complete follow up surveys every 3 months |
|  |  | Routine clinic data | Clinic notes and viral load results will be abstracted from the charts and electronic medical records repositories for all AYHIV (~2400) ages 16-24 years in the 30 clinics |
| AIM 2: Assess implementation and service outcomes and determinants of implementation |  | FGDs with providers | Up to 30 with 7-10 participants each from the intervention and control facilities ≥18 years old |
|  |  | IDIs with providers | Up to 6 IDIs with providers from each participating clinic |
|  |  | FGDs with AYHIV | Up to 30 with 7-10 participants 16-24 years each from intervention facilities |
|  |  | Competence assessments using the ENACT tool | Up to 90 trained providers ≥18 years old at the 15 intervention clinics |
|  |  | Fidelity assessments using a standardized checklist | Up to 90 trained providers ≥18 years old at the 15 intervention clinics |
|  |  | Quantitative surveys with AYHIV | ~600 AYHIV involved in the intervention |
|  |  | Routine clinic records for AYHIV | All AYHIV in the 30 clinics ages 16-24 years |
|  |  | Checklist in the patient chart | All AYHIV (~2400) AYHIV 16-24 years in the study sites |
|  |  | Quantitative survey with facility/HIV clinic heads | 30 facility/ HIV clinic heads from selected study sites |
|  |  | Quantitative surveys with providers | Up to 6 providers from each of the 30 selected study sites |
| Aim 3: Conduct an economic evaluation of the intervention |  | Time in motion studies for provider time | Providers in the 30 adolescent HIV clinics |
|  |  | Interviews with program officers with information on program administration | 30 program officers in the HIV clinics |
|  |  | Quantitative surveys with AYHIV | ~600 AYHIV involved in the intervention |

